### Outcome measures

All assessments take place on the online platform. The primary outcome of the effectiveness analyses is physical activity as broader construct which ensures comparability with other studies [40]. Secondary outcomes are outcomes more closely related to the intervention (exercise, motivational and volitional determinants of exercise) as well as quality of life and depressive symptoms (see Table 2 for an overview).

**Table 2 Tab2:** SPIRIT figure and overview of measures

TIMEPOINT	Measures	Enrolment (T0)	Baseline (T1)	Allocation	Post-Treatment (T2)	Follow-Up (T3)
ENROLMENT:						
Informed consent		x				
Eligibility screen			x			
Randomization				x		
INTERVENTIONS:						
Intervention group (web-based intervention)						
Control group						
ASSESSMENTS:						
Physical activity	IPAQ-SF [41]		x		x	x
Amount of exercise	BSA [42]		x		x	x
Intention strength	[43]		x		x	x
Outcome expectations	[43, 44]		x		x	x
Self-efficacy (motivational, maintenance, recovery)	[45]		x		x	x
Risk perception	[24]		x		x	x
Action planning	[43]		x		x	x
Coping planning	[25]		x		x	x
Situational barriers	[25]		x		x	x
Social support	[46]		x		x	x
Depressive symptoms	CES-D [47]		x		x	x
Quality of life	WHOQOL-BREF [48]		x		x	x
Sociodemographics	[49]		x			
Stage of change	[50]		x			
Self-control competence	VCQ (subscales planning and spontaneity [51])		x			

#### Primary outcome

Physical activity is assessed using the International Physical Activity Questionnaire – Short Form (IPAQ-SF, German short version; [41]). Seven items measure on how many days and in what extent vigorous activity, moderate activity and walking activity were performed during the last 7 days. For generating the total physical activity score (Met-minutes/week), the IPAQ protocol is used. The validity of the IPAQ is good and its retest reliability is .80 [52].

#### Secondary outcomes

*Amount of exercise* is measured with the Physical Activity, Exercise, and Sport Questionnaire (German acronym BSA “Bewegungs- und Sportaktivitätsfragebogen” [42]). Participants indicate if they performed one or more exercise activities within the last 4 weeks. They can specify up to three different activities as well as the frequency (monthly) and the duration (of each episode) of the activity. The calculated BSA score reflects the weekly amount of exercise.

*Intention strength* is assessed using the item “How strong is your intention to exercise regularly during the next 4 weeks” [43]. Response format is on a six-point scale ranging from 0 (“not at all”) to 5 (“very strong”).

*Positive and negative outcome expectations* regarding exercise are assessed using existing scales [43, 44] adjusted to our sample of young adults. More precisely, we excluded all items targeting specifically orthopaedic patients. Ten negative outcome expectations (e.g. “If I exercise regularly, I could hurt myself”) and nine positive outcome expectations (e.g. “If I exercise regularly, I become more confident”) are cumulated into one score. Response format of the items is on a four-point scale ranging from 1 (“I do not agree”) to 4 (“I agree”).

*Motivational self-efficacy* is measured using the item “I am confident that I will be exercising regularly in the next 4 weeks” [24]. Response format is on a four-point scale (1=”I don’t agree” to 4=”I agree). Accordingly, the two facets of *volitional self-efficacy* are measured using the same item format. *Maintenance self-efficacy* is assessed with the item: “I am confident that I will exercise regularly even if it takes some time until it becomes a routine” [24]. *Recovery self-efficacy* is assessed with the item: “I am confident that I am able to resume my regular exercise, even if I have relapsed several times” [24].

*Risk perception* is measured with three items that are cumulated into a mean score [24]. Each item assesses the agreement to the following statement: “The likelihood that I develop a [cardiovascular disease / orthopaedic diseases / metabolic disease] is high”. Response format is on a four-point scale ranging from 1 (“I do not agree”) to 4 (“I agree”).

*Action planning* is assessed by asking the participants if they already have a detailed plan on when, where, how, with whom and how often they will execute their exercise activities [43]. A sum score ranging from 0 to 10 is calculated by adding up the positive answers for two activities.

*Situational barriers* are assessed with the barrier scale of Krämer and Fuchs [25]. Based on the mean score of 17 items, it is measured how many internal barriers (e.g. “I was tired”) and external barriers (e.g. “the weather was bad”) the participant experienced within the last 4 weeks (1 = “not at all” to 4 = “very much”). All items were introduced by the phrase: ‘How strongly did the following situations keep you from exercising within the last 4 weeks?’ Responses were given on a four-point scale ranging from 1 (‘not at all’) to 4 (‘very much’).

*Coping planning* is assessed with the barrier management scale of Krämer and Fuchs [25]. 15 items are used to assess the coping strategies that participants use in order to exercise despite situational barriers. The launching phrase (“In order to stick to your scheduled exercise program…”) is followed by 15 possibilities to deal with barriers (e.g. “…, I remind myself of the benefits of exercising”). Participants report for each item to what degree they agree with the statement (1=”I do not agree” to 4 = “I agree”). A mean score of the items is calculated.

*Action control* covers three facets [24]: self-monitoring is assessed with the item “I have regularly monitored whether I exercised enough”. Awareness of standards is assessed with the item: “I have often thought of my exercise intention”. Self-regulatory effort is assessed with the item “I have taken care to exercise as much as I had intended”. The response format is on a four-point scale ranging from 1 (“I don’t agree”) to 4 (“I agree”).

*Social support* regarding exercise is assessed using the scale developed by Fuchs [46]. The launching phrase (“People in my social environment…”) is followed by seven different items (e.g. “… exercise with me”). Response format is on a four-point scale ranging from “(almost) never” to “(almost) always”.

*Depressive symptoms* are assessed with the Center for Epidemiologic Studies Depression Scale (CES-D scale, German version by [47]). The CES-D scale consists of 20 depressive symptoms that are rated on a four-point scale (0=“rarely or not at all”; 1=“sometimes”; 2=“often”; 3=“most of the time”).

*Quality of life* is assessed with the short version of the World Health Organization Quality of Life Scale (WHOQOL-BREF [48]). It consists of 26 items that are covering four different quality of life domains. In this study, we only investigate three domains: physical health (e.g. “Do you have enough energy for everyday life?”), psychological health (e.g. “How much do you enjoy life?”) and social relationships (e.g. “How satisfied are you with your personal relationships”). The domain “environment” is not relevant for our sample and therefore is not assessed in favour of conciseness of the questionnaire. The 26 items are rated on a five-point scale for the last 2 weeks [48]. Three domain scores will be calculated.

#### Sample characteristics

*Sociodemographic characteristics* (e.g. age, gender, height, weight, marital status) are assessed according to the recommendations of Deck and Röckelein [49]. *Stage of change* is assessed with a single item [50]. *Self-regulatory competencies* is covered using the subscales planning and spontaneity of the Volitional Components Questionnaire (VCQ [51]).

### Statistical analyses

According to CONSORT statement [32], sample characteristics of both subgroups will be contrasted descriptively in order to detect relevant differences between the two samples. All analyses for the primary and secondary outcomes will be performed with an alpha level of 5% which means that the analyses for secondary analyses will be explorative. Outcome analyses will follow an intention-to-treat principle by including all randomized participants into the analyses. Outcomes will be analysed using a linear mixed model handling missing data under the assumption that data are missing at random. All participants and data points will be included in the mixed model analyses. The mixed model for the primary outcome (physical activity) will include group, time, and the interaction of group and time as fixed effects and participant and university as random effect. Analyses will use restricted maximum likelihood estimation (REML). For repeated measures (time), an autoregressive covariance structure with heterogeneous variances is assumed. Secondary outcomes will be analysed accordingly. We will calculate between-group effect sizes for the outcomes using the post-intervention estimated means and their pooled observed standard deviation. Additional per protocol analyses will include only those participants completing all three assessments (IG and CG) and at least three intervention modules (IG). For the main outcome, potential moderators will be analysed exploratively by including the following variables and all possible interactions in the mixed model: gender, body mass index, depressive symptoms, self-control competence and recruiting season (separate mixed model for each moderator). All analyses will be conducted using IBM SPSS.

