**Methods:**

A two-armed randomized controlled trial (RCT) of parallel design is conducted. Participants are recruited via the internet platform StudiCare (www.studicare.com). After the baseline assessment (t1), participants are randomized to either intervention group (immediate access to web-based intervention) or control group (access only after follow-up assessment). Four weeks later, post-assessment (t2) is performed in both groups followed by a follow-up assessment (t3) 3 months later. Assessments take place online. Main outcome analyses will follow an intention-to-treat principle by including all randomized participants into the analyses. Outcomes will be analysed using a linear mixed model, assuming data are missing at random. The mixed model will include group, time, and the interaction of group and time as fixed effects and participant and university as random effect.

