### Proposed sample size

The sample size calculation is based on the difference in change in the primary outcome (physical activity) from pre- to post-assessment in both treatment arms (intention-to-treat analyses). Based on previous studies on web-based physical activity interventions in students, mean effect sizes of around d = 0.5 are expected in per-protocol analyses [18, 22, 39]. In order to detect such intervention effects in two-sided significance testing (α = .05) with a power of 80%, a sample size of 128 participants is required. Taking into account an expected study drop-out of about 20%, 160 participants must be included in the study. This sample constitutes the ITT sample. Adjustment for baseline physical activity scores will further improve the power of the primary comparison.

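### The sample-size section promises a power gain from baseline adjustment, but the stated primary model contains no such adjustment

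*Protocol article*

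**What the plan says.** The section Proposed sample size says that the calculation is "based on the difference in change in the primary outcome (physical activity) from pre- to post-assessment". It states that "mean effect sizes of around d = 0.5 are expected in per-protocol analyses" and concludes that "with a power of 80%, a sample size of 128 participants is required". It then adds: "Taking into account an expected study drop-out of about 20%, 160 participants must be included in the study". The section ends: "Adjustment for baseline physical activity scores will further improve the power of the primary comparison".

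The section Statistical analyses says that the model for the primary outcome "will include group, time, and the interaction of group and time as fixed effects and participant and university as random effect". It includes all participants and all data points, treats time as the repeated factor, and assumes an autoregressive covariance with heterogeneous variances. The abstract lists the same terms. Neither place mentions a baseline covariate or a constraint of equal baseline means, and baseline activity is not among the listed moderators. Effect sizes are to use the post-intervention estimated means and their pooled observed SD.

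On timing, the abstract says: "After the baseline assessment (t1), participants are randomized to either intervention group".

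**The concern.** The two sections describe different primary analyses. Having the t1 score in the model as a response is not the same as adjusting for it. When each arm has its own free mean at each time, the interaction at t2 subtracts the whole observed baseline difference. A baseline-adjusted contrast subtracts only the part that predicts t2.

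Two things are at stake:

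- **Efficiency.** The gain that the sample-size section counts on does not come from adjustment, because the model has none.
- **Prespecification.** With equal variances, a chance baseline imbalance enters the change contrast with coefficient -1 and the adjusted contrast with coefficient -rho (rho is the t1-t2 correlation). The two can therefore give different estimates and p-values from the same data. The analyst blinding described in the protocol relies on syntax written before the treatment variable is added, so the choice of estimator should be settled by then.

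**Working it through.** **Inputs from the protocol article.** Two-sided alpha 0.05, power 80%, d = 0.5, 128 evaluable (64 per arm at 1:1), 20% drop-out, 160 randomised. Not given: rho, and whether d is standardised by the raw outcome SD or the change-score SD. The only related figure is the IPAQ retest reliability of .80. That is not a 4-week pre-post correlation in this sample, so a range is shown.

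**Step 1: reproduce the stated figure.** A two-sample t test (non-central t) with d = 0.5 needs 64 per arm, 128 in total, with power 80.1%. Drop-out: 128 / 0.80 = 160. Both figures reproduce with no allowance for baseline adjustment.

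**Step 2: what the written model estimates.** The group-by-time means are saturated. With complete data the t2 interaction is therefore the difference in mean change, whatever the within-participant covariance. In a simulated data set with unequal variances, the generalised least squares interaction and the plain difference in mean change were both 0.40146.

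**Step 3: variances.** Let s1 and s2 be the SDs at t1 and t2. Per participant:

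- change: s1² + s2² - 2·rho·s1·s2
- baseline-adjusted: s2²(1 - rho²)
- change minus adjusted: (s1 - rho·s2)²

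The last line is never negative, so the written contrast is never more efficient. It is zero when s2/s1 = 1/rho. For example, at rho = 0.8 and s2/s1 = 1.25 both variances are 0.5625 (with s1 = 1), a tie.

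With s1 = s2 = 1 the factors are 2(1 - rho) and 1 - rho², and their ratio is 2/(1 + rho). Against a comparison of t2 scores alone, the change contrast breaks even at rho = s1/(2·s2). That is 0.5 with equal SDs and about 0.42 at s2/s1 = 1.2.

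**Step 4: power with d on the raw outcome SD.** Non-central t, 64 per arm, equal variances. The effective d is 0.5/√(2(1 - rho)) as written and 0.5/√(1 - rho²) adjusted.

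| rho | variance factor, written | variance factor, adjusted | power, written | power, adjusted |
|---|---|---|---|---|
| 0.3 | 1.40 | 0.91 | 66% | 84% |
| 0.5 | 1.00 | 0.75 | 80% | 90% |
| 0.7 | 0.60 | 0.51 | 95% | 98% |
| 0.8 | 0.40 | 0.36 | 99.3% | 99.7% |

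At rho = 0.5 the adjusted analysis needs 128 × 0.75 = 96 evaluable participants to match the written model with 128.

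**Step 5: power with d on the change-score SD.** The written model has 80% at every rho. The adjusted variance relative to change is (1 - rho²)/(2(1 - rho)) = (1 + rho)/2, so the effective d is 0.5/√((1 + rho)/2). Adjusted power is about 84% at rho = 0.8, 90% at 0.5 and 95% at 0.2.

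**Step 6: drop-out.** Take 80 randomised per arm, of whom 20% have t1 only, with unit SDs and rho = 0.3. Completers' change scores have variance 1.4 × 2/64 = 0.0438. The mixed model's interaction has 0.0407, so it recovers a little. The adjusted contrast has 0.91 × 2/64 = 0.0284.

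**The case against.** The strongest case against is that this is a wording mismatch around a standard and valid analysis. Most of it stands:

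- The sample size takes no credit for adjustment, and the change contrast is unbiased under randomisation.
- A reader might infer that the trial falls below 80% power. The documents do not show this. It requires d on the raw SD and rho below the break-even value. The effect-size definition in Statistical analyses favours the raw SD, but the sample-size wording about a difference in change allows the change-score SD, and then nothing is lost.
- A reader might infer that using t1 as a response gains nothing. Above break-even it does gain over a comparison of t2 scores alone, only less than adjustment would.
- A reader might infer that the written model is less efficient at every correlation below 1. Under the heterogeneous variances that the protocol assumes, the two can tie.
- The primary contrast is not named. The sample-size section points to the difference in change. If the test were instead the t2 difference in estimated means, complete data would make it a post-only comparison, which is also unadjusted.
- Equality with change scores is exact only for complete data. It is approximate under drop-out, or if the arms are unbalanced across universities.

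The argument that an unseen analysis plan may settle the matter does not remove the mismatch. The article itself states the model terms, twice, and they do not contain what its sample-size section promises.

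**Conclusion.** The point holds as an internal contradiction with a likely loss of efficiency of unknown size. The primary model as written has no baseline adjustment, so the further gain stated in the sample-size section does not follow from it. If d is on the raw SD and variances are equal, the gap to an adjusted analysis is about 18 percentage points of power at rho = 0.3, 10 at 0.5, 2 at 0.7 and under 1 at 0.8. If d is on the change-score SD, the planned 80% is kept and the gain forgone runs from about 4 points (rho = 0.8) to 15 (rho = 0.2). This is neither a validity error nor an error in the 128 or 160. Severity is moderate.

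**What to change.** Make the Statistical analyses section, and the abstract with it, agree with the sample-size section. Either of two forms does this:

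- **Equal baseline means.** Keep t1, t2 and t3 as responses. Fit time plus group × t2 and group × t3, with no group effect at t1. This is valid because randomisation follows t1, and it keeps every randomised participant with a t1 score.
- **Baseline as covariate.** Model t2 and t3 as responses, with the t1 score and t1 × time as covariates.

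In either form, name the group effect at t2 as the primary contrast and treat the secondary outcomes in the same way. If the written model is kept, delete the sentence on the power gain from the sample-size section and state which contrast is primary.

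The cost is a sentence or two of text and a change to the SPSS syntax, made before the treatment variable is added. No new data are needed, since the IPAQ-SF is already scheduled at t1.

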## Methods

### Design

A two-armed randomized controlled trial (RCT) of parallel design is conducted in order to investigate the research questions. Participants are recruited via the internet platform StudiCare (www.studicare.com). All students registering for the study and giving informed consent have access to the baseline assessment (t1). Individuals fulfilling inclusion criteria (student status, older than 18 years, exercising less than three times a week) are randomized to either the intervention group or the control group. There are no further exclusion criteria in order to enable as many students as possible to engage in the training and to achieve a high external validity. Participants in the intervention condition will immediately receive access data for the web-based intervention, while participants in the control group do not receive the intervention until follow-up assessment (t3). For the control group access to the web-based intervention is activated after completing the follow-up assessment (t3). After 4 weeks, post-assessment (t2) is performed in both groups followed by a follow-up assessment (t3) 3 months later.

The RCT is conducted in accordance with the CONSORT 2010 Statement [32] and the extension of the CONSORT Statement for pragmatic effectiveness studies [33]. The documentation of the intervention follows the guidelines for implementation and documentation of web-based intervention studies [34]. The study has been approved by the data protection office and the ethics committee of the University of Freiburg (No.: 504/18) and the trial is registered in the German clinical trials register under DRKS00016889. With respect to trial auditing, the Project Management Group ([name], JB) meets weekly over the course of the trial to oversee conduct and progress of recruitment. An independent data monitoring committee is not implemented, as “InterAKTIV Sport” is a low-risk intervention. Deviations from the study protocol will be fully documented and disclosed in further publications. In case of deviations, the protocol in the clinical trial registry will be updated.

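### The autoregressive covariance gives the 4-week and 3-month gaps the same lag correlation without justification, so standard errors may be misstated; an unstructured 3 x 3 matrix avoids this cheaply

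*Protocol article*

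**What the plan says.** The Statistical analyses section of the protocol article specifies a linear mixed model, fitted by REML in SPSS, with "group, time, and the interaction of group and time as fixed effects and participant and university as random effect". It adds: "For repeated measures (time), an autoregressive covariance structure with heterogeneous variances is assumed". No reason is given for the autoregressive choice, and no version scaled to elapsed time is mentioned.

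The visit schedule is in the Design section: "After 4 weeks, post-assessment (t2) is performed in both groups followed by a follow-up assessment (t3) 3 months later". The Proposed sample size section bases the calculation on the "difference in change in the primary outcome (physical activity) from pre- to post-assessment in both treatment arms", so the t1–t2 contrast is the powered one. The end of the Background section also expects a benefit at the 3-month follow-up, so the t1–t3 contrast matters too.

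No correlation between visits is given by interval. The only related figure is a retest reliability of .80 for the activity questionnaire (Primary outcome section), without its interval.

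**The concern.** A first-order autoregressive structure indexes visits by order. It sets the residual correlation to ρ for t1–t2, ρ for t2–t3 and ρ² for t1–t3. With 3 months taken as about 13 weeks, the second gap is 13/4 = 3.25 times the first. An autoregressive structure is chosen because correlation is expected to fall with time. If it does, two gaps this different would not be expected to share one correlation.

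The fit then compromises between the short-gap and the long-gap correlation. If the t1–t2 correlation is understated, the standard error of the t1–t2 change comes out too large. For t1–t3 the error can run the other way. At stake are the tests of the powered contrast and of the follow-up contrast. With complete data and all group-by-time means in the model, the point estimates do not depend on the covariance choice.

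**Working it through.** **1. The plan's own figure.** With d = 0.5, two-sided α = .05 and 80% power, the normal approximation gives n per arm = 2 × (1.96 + 0.84)² / 0.5² = 62.7, so 63. The t-test calculation gives 63.77, so 64 per arm and 128 in total. Allowing for 20% drop-out, 128 / 0.80 = 160. Both figures reproduce, and neither depends on the covariance structure.

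**2. The planned covariance.** With a participant intercept of variance τ² and visit-specific residual SDs σ₁, σ₂, σ₃:

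- variance at visit i = τ² + σᵢ²
- cov(t1,t2) = τ² + σ₁σ₂ρ
- cov(t2,t3) = τ² + σ₂σ₃ρ
- cov(t1,t3) = τ² + σ₁σ₃ρ²

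That is five parameters for a matrix with six free entries. With equal variances it forces corr(t1,t2) = corr(t2,t3). With unequal variances the two can differ, but only by way of the visit variances.

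**3. The check.** For an assumed true matrix T, find the planned-form matrix S that minimises log|S| + trace(S⁻¹T), the large-sample best fit. Compare the SD of change under S with that under T. The ratio R is model SE / true SE. Actual type I error = 2 × [1 − Φ(1.96 × R)]. The university effect is left out. All correlations below are assumptions. Results are for random intercept plus first-order heterogeneous autoregression, true variances equal, complete data:

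| Assumed r(t1,t2), r(t2,t3), r(t1,t3) | R for t1–t2 | R for t1–t3 |
|---|---|---|
| .50, .50, .50 (equal) | 1.00 | 1.00 |
| .50, .50, .25 (autoregressive by visit order) | 1.00 | 1.00 |
| .60, .57, .55 | 1.01 | 1.00 |
| .80, .72, .70 | 1.03 | 0.99 |
| .60, .50, .45 | 1.04 | 1.00 |
| .70, .50, .50 | 1.06 | 0.99 |
| .60, .30, .30 | 1.11 | 0.98 |
| .80, .48, .39 (pure decay) | 1.08 | 0.95 |
| .70, .31, .22 (pure decay) | 1.23 | 0.97 |

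The pure-decay rows raise the 4-week correlation to the powers 13/4 = 3.25 and 17/4 = 4.25; for example .7^3.25 = .31 and .7^4.25 = .22. For 4-week correlations of .5 to .8, R for t1–t2 runs from 1.08 to 1.23. Without the participant intercept it would be 1.16 to 1.29.

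**4. What the ratios mean.**

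- t1–t2, R = 1.035: type I error 2 × [1 − Φ(2.03)] = 4.2%.
- t1–t2, R = 1.11: 2 × [1 − Φ(2.18)] = 2.9%.
- t1–t2, R = 1.23: 2 × [1 − Φ(2.42)] = 1.6%.
- t1–t3, R = 0.947: 2 × [1 − Φ(1.86)] = 6.3%.

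If true power for t1–t2 were exactly 80%, model-based power = 1 − Φ(1.96 × R − 2.80): 78% at R = 1.035 and 73% at R = 1.11.

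**5. Sensitivity.** With 20% random drop-out (10% after t1, 10% after t2) the pattern is the same; for .60, .30, .30 the ratios are 1.10 and 0.99. With equal correlations of .50 but SDs of 1, 1.2 and 1.2, they are 0.98 and 1.00.

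**6. Unstructured matrix.** Six parameters, no relation imposed between correlations: R = 1.00 in large samples for every pattern tried.

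**The case against.** The strongest reply is that unequal spacing does not by itself make the structure wrong. The planned model is more than a bare autoregression: it has a participant intercept and a separate variance at each visit. Where activity has a stable between-person component, these absorb much of the misfit, and with mild decay the t1–t2 standard error is off by only about 1–4%. The larger figures assume that all correlation decays exponentially. For the powered contrast the error in the decaying cases is conservative. All of this stands, and it keeps the point modest.

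Three stronger readings are tempting, and the documents do not support them.

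- **That the standard errors are wrong.** This needs the true correlations, which the article does not give by interval. Two of the patterns above show no error at all.
- **That power falls to about 65%.** This follows only from the most extreme pattern and from fixing true power at exactly 80%. The sample size section does not say which SD standardises d = 0.5. If it is the raw SD, with 64 per arm and correlations .70, .31, .22, the SD of change is √(2 × 0.30) = 0.775. The standardised difference is then 0.5 / 0.775 × √32 = 3.65. True power is Φ(3.65 − 1.96) = 95.5%, and model-based power is Φ(3.65 − 1.96 × 1.233) = 89%, still above the planned 80%.
- **That the model will probably not converge.** Five parameters for six entries is not over-parameterised, and nothing was simulated to show a failure.

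**Conclusion.** The point holds in conditional form. As written, and read as first-order, the covariance gives one lag correlation to gaps that differ about threefold, and the article offers no reason for it. If correlation decays with elapsed time, the t1–t2 standard error is about 3–11% too large under mild to moderate decay and up to about 23% too large under pure exponential decay, with some loss of power. The t1–t3 standard error is up to about 5% too small, with type I error up to about 6.3%. There is no error if the three correlations and the variances are equal, and about 2% on t1–t2 in the unequal-variance case tried.

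These sizes rest on assumed correlations, a large-sample fit, the first-order reading and 3 months taken as 13 weeks. This is an avoidable modelling assumption in the primary analysis, not a demonstrated error. The sample size is not touched. The change is worth making because it removes the possible misstatement whatever the true correlations are.

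**What to change.** In the Statistical analyses section, replace the autoregressive structure with an unstructured 3 x 3 covariance for the repeated measures. Drop the participant random intercept: its variance adds the same constant to all six entries of an unstructured matrix, so the two cannot be separately identified. Keep the university random effect. Name in advance one fallback that does not rely on equal spacing, for example heterogeneous compound symmetry or a structure based on actual elapsed time. Apply the same wording to the secondary outcomes, which are to be analysed in the same way.

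The cost is one sentence, one changed model option and one extra covariance parameter (six instead of five), with 160 participants planned. The change should be made and documented before the treatment variable is added to the data set.

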Based on the HAPA, we developed a web-based psychological training called ‘InterAKTIV Sport’ (German title). The training consists of several web-based self-help modules targeting at motivational and volitional competences (cf. methods section). It aims at promoting exercise behaviour as a subset of physical activity. Physical activity is defined as any (physical) activity that requires energy and is caused by the skeletal muscles [10]. Exercise, on the other hand, covers only those physical activities that are structured, planned and repetitive with the goal of improving or maintaining physical fitness [10]. The intervention focuses concisely on exercise, as exercise is supposed to be more tangible for young adults than “physical activity” in general. Many students are familiar with exercise groups and clubs from their adolescence, but often they lost their relatedness when transiting into student life [31].

The study aims at investigating the effects of the web-based HAPA intervention on physical activity in students (primary outcome). We expect that participants of the intervention group will be more physically active than a waitlist control group at post-intervention and 3 months follow-up. Additionally, we investigate the effects of the intervention on motivational and volitional variables proposed by the HAPA model (secondary outcomes). Quality of life and depressive symptoms are investigated with an explorative approach.

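### The effect size is built from post-intervention means of a model with no listed baseline adjustment, although the sample size section promises one; d is noisier than it need be and can drift from the group-by-time result

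*Protocol article*

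**What the plan says.** All places are in the protocol article.

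- **Statistical analyses, effect size:** "We will calculate between-group effect sizes for the outcomes using the post-intervention estimated means and their pooled observed standard deviation".
- **Statistical analyses, model:** the primary model "will include group, time, and the interaction of group and time as fixed effects and participant and university as random effect". No baseline covariate is named. The section adds: "All participants and data points will be included in the mixed model analyses". The natural reading is that t1 is one of the levels of time.
- **Proposed sample size, target:** the calculation is "based on the difference in change in the primary outcome (physical activity) from pre- to post-assessment", with a planning value of d = 0.5.
- **Proposed sample size, adjustment:** "Adjustment for baseline physical activity scores will further improve the power of the primary comparison".
- **Background, aims:** the hypothesis is worded in levels, namely that "participants of the intervention group will be more physically active than a waitlist control group at post-intervention and 3 months follow-up".
- **Abstract:** the primary outcome is described as change in physical activity.

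**The concern.** Two sections describe the primary comparison differently. The sample size section speaks of change and of adjustment for baseline. The analysis section lists a model in which each arm has its own free mean at t1, t2 and t3, and then takes the effect size from the t2 means alone. In such a model the estimated t2 means are not corrected for a difference that was already there at t1.

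Randomisation is in permuted blocks, with no stratification by baseline activity described, so some chance difference in a variable quantity such as weekly MET-minutes is to be expected. Part of it then enters d. The group-by-time contrast at t2 subtracts the baseline difference, so the two results need not tell the same story. The same effect size rule is written for the outcomes in general, so secondary outcomes inherit the problem. Readers and later meta-analyses are likely to take up the effect size.

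**Working it through.** **Inputs.** From the protocol: d = 0.5, two-sided alpha 0.05, power 80%, 128 analysable and 160 randomised participants (Proposed sample size); 1:1 allocation (Randomization and blinding), hence 80 per arm. Assumed: the baseline-to-post correlation r, taken from 0.4 to 0.8. The upper end borrows the retest reliability of .80 quoted under Primary outcome, which is not a four-week correlation within a trial.

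**1. The plan's own figure.** A two-sample t-test at d = 0.5 needs 63.77, so 64 per arm, 128 in total; 128 / 0.80 = 160. Both stated figures reproduce, and the point does not touch them.

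**2. Chance baseline difference.** SE = sqrt(2/80) = 0.158 SD. The 95% range is ±1.96 × 0.158 = ±0.31 SD. A difference beyond 0.2 SD in either direction occurs in about 21% of trials.

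**3. Carry-over into the post difference.** Given a baseline difference b, the expected shift is r × b in the post difference and −(1 − r) × b in the difference in change. At b = 0.31 SD:

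| r (assumed) | shift in post difference | shift in difference in change |
|---|---|---|
| 0.4 | 0.12 | −0.19 |
| 0.5 | 0.16 | −0.16 |
| 0.6 | 0.19 | −0.12 |
| 0.8 | 0.25 | −0.06 |

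The post difference thus moves by a quarter to a half of the planned 0.5. The gap between the two contrasts is b itself.

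**4. Check in the listed type of model.** A three-time-point group-by-time model was simulated with autoregressive correlation 0.8 (covariance taken as known), 80 per arm and 20% drop-out. The modelled baseline difference equalled the raw one. The estimated t2 difference moved by 0.77 SD per 1 SD of baseline difference, close to r. Fitting the mixed model does not by itself remove the imbalance.

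**5. Same target on average.** In simulation both contrasts averaged 0.50 when the true effect was 0.5, and 0.30 when it was 0.3.

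**6. What adjustment gains.** With complete data, the SE of the unadjusted post difference is 0.158 SD. The baseline-adjusted difference has SE 0.158 × sqrt(1 − r²): 0.137 at r = 0.5 and 0.095 at r = 0.8. The difference in change has SE 0.158 × sqrt(2(1 − r)): 0.158 at r = 0.5 and 0.100 at r = 0.8. The adjusted contrast is the most precise of the three at either value.

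**The case against.** - **The baseline adjustment may already be intended.** The sample size section says so. If the adjustment is in the fitted model, the estimated post means are adjusted and the problem largely disappears. This stands as a qualification, but the model as listed omits it, and the two sections cannot both be followed as written.
- **The tested contrast is never named, and the aims speak of levels.** Correct. That the test is the group-by-time contrast is inferred from the interaction term, the sample size text and the abstract. A post-mean d does fit the wording of the aims.
- **A reader might infer that d estimates something other than what was planned, or is biased.** The documents do not support this. Under randomisation, and without selective drop-out, the two differences have the same expectation (step 5). The cost is noise and inconsistency in one realised trial.
- **A reader might also infer that a large d with a non-significant interaction, or a d near zero with a significant one, is a likely result.** It is uncommon. With 64 per arm, a true effect of 0.5 and r from 0.4 to 0.8, a significant change contrast with an absolute d below 0.1 occurs in 0.2 to 1.1% of trials, and a non-significant one with d of at least 0.5 in 0.1 to 6.0%. At a true effect of 0.3 the figures are 0.8 to 7.0% and 1.3 to 3.8%.
- **A raw change contrast is no cure.** True: it carries imbalance in the other direction and is less precise than the post difference when r is below 0.5. Hence the case for an adjusted contrast.
- **The denominator, the three-month effect size and a confidence interval.** A pooled post-assessment SD is conventional. A baseline SD has its own weakness, since eligibility requires exercising less than three times a week and may narrow the baseline spread. An effect size at follow-up and an interval are details that an article may leave to the full plan. None of these is part of the point.

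**Conclusion.** The point holds in a limited form. The effect size rule draws on means from a model that lists no baseline adjustment, while the sample size section promises that adjustment and plans on the difference in change. The resulting d is unbiased on average but carries about r times the chance baseline difference: a 95% range of about ±0.16 SD at r = 0.5 to ±0.25 SD at r = 0.8, against a planned d of 0.5. It can therefore diverge from the group-by-time result.

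This rests on three assumptions: t1 enters as a level of time, the model is fitted as listed, and r lies in the assumed range. The sample size and the type I error of the primary test are unaffected. It is a moderate matter of reporting and consistency, worth correcting because the remedy uses data already collected.

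**What to change.** Reconcile Proposed sample size with Statistical analyses by writing the baseline adjustment into the primary model. Either of two forms will do:

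1. Keep t1 as an outcome and constrain the baseline means to be equal across arms, by leaving out the group main effect at t1. This retains every randomised participant with a baseline score, in line with the stated aim of using all participants and data points.
2. Use the baseline score as a covariate, with t2 and t3 as the outcomes. Participants with neither later assessment then contribute nothing to the comparison.

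Name the group difference at t2 from that model as the tested contrast, and compute d from the same difference. Test and effect size then rest on one quantity. Treat the secondary outcomes in the same way. The sponsor may choose the standardising SD, provided it is fixed before the treatment variable is added to the data set.

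Cost: a sentence or two in the analysis section and a small change to the analysis syntax. No new data and no change to the 160 participants.
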